#### Recruitment

The participants will be recruited from ten centres of Amcha in Israel. Mean age of Holocaust survivors attending the social club at Amcha centres is currently (in the year 2020) 89 years, the youngest were born in 1945. About 30% were born between 1935 and 1945 (now 75–85 years old), 50% between 1925 and 1935 (now 85–95 years old) and 20% were born before 1925 (now over 95 years old).

Study participants will be recruited from current and new social club members. During the time of the research project, there will be active advertisements in the community and at medical practices in order to introduce Amcha, its social clubs and the study treatment. The fact that Amcha is present in 15 cities across Israel, has a very good reputation in the country, and is working with other medical institutions, makes the proposed study highly feasible.

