#### Sample size

Previous studies on PTSD treatments found a large mean effect size for PTSD outcomes (controlled *d* = 0.8 with a supportive control group) [26]. Studies on LRT also found a large mean (pre-post) effect size in older individuals with a mental disorder (in most studies depression) (g = 1.3; 19). We rest our sample size calculation on the conservative assumption of a medium-to-large effect size (d = 0.7, corresponds to f = 0.35). The sample size was calculated using G*Power 3.1.0 [27]. Given an α = 0.05 and a test power 1-β = 0.80, a total sample size of *n* = 50 (each group *n* = 25) is required. We assume a rather conservative drop-out rate of about 40% from enrolment to follow-up. Thus, we propose to start with 80 participants at enrolment (i.e. 40 in the LRT and 40 in the control group).

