Standardization of procedures: Therapists use a manual of this LRT-HS, which includes descriptions of the content of each session and material for the sessions. Because of the research setting, therapists will document what happens during the sessions in detail on checklists, i.e. which interventions they had applied and whether (and why) they had stressed one point more than another. Working sheets and interview guidelines are included in the manual as well. Adherence to the treatment manual is ensured by the intensive training before the intervention phase, the regular supervision and the examination of the session documentations.

Psychotherapists: The LRT-HS will be administered by trained psychotherapists, i.e. psychologists, psychiatrists and clinical social workers. All psychotherapists have a master’s degree in psychology, medicine or clinical social work. Furthermore, all participating psychotherapists will be trained for this intervention by a panel of experts and supervisors in the field of psychotherapy for older age (Dr. [name], Dr. [name], Dr. [name], Dr. [name]). A two-day workshop will precede the intervention phase. Supervision sessions will take part every month (i.e. about 5 sessions per patient). All sessions will be documented in a structured form and will be reflected upon in the supervision sessions.

Pilot data: We applied the described treatment programme with a few participants and found that they accepted it and rate the treatment as very helpful. In addition, symptoms were reduced to a clinically significant degree.

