### Data analysis

#### Statistical analysis

Several analytic strategies are planned to test the efficacy of the treatment. First, analyses of variance (ANOVAs) will be conducted to compare the mean outcome in PTSD and depressive symptoms (primary endpoints) as well as the secondary endpoints. The age at the time of trauma, gender, educational level, cognitive status and trauma severity will be considered as covariates.

Secondly, individual growth curves will be analysed, i.e. rates and shapes of change will be examined, and individual growth curves will be compared to investigate differences.

Thirdly, multivariate analyses will be used to test the effect of the treatment with regard to primary and secondary outcomes. In this way, correlations between the outcome measures can be considered. Post hoc analyses will be performed following a significant overall effect.

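### The named efficacy analysis makes no allowance for therapist clustering in the LRT arm, so its standard error is too small if therapists differ and treat more than one participant each

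*Protocol article*

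**What the plan says.** On delivery, the Life-review therapy section of the protocol article states: "The LRT-HS will be administered by trained psychotherapists, i.e. psychologists, psychiatrists and clinical social workers". The inclusion criteria bar other individual psychotherapy and exempt LRT from that bar, so LRT is one-to-one. The Supportive control group section describes a group-format social club run by staff who are separate from the LRT therapists. Allocation is individual and 1:1 (Randomisation). On sites: "The participants will be recruited from ten centres of Amcha in Israel".

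On analysis, the Statistical analysis section names ANOVAs for the primary and secondary endpoints and adds: "The age at the time of trauma, gender, educational level, cognitive status and trauma severity will be considered as covariates". Individual growth curves and multivariate analyses follow. As described, these deal with change within a person and with correlation between outcomes. Neither is given a therapist level.

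On size, the target rests on a "medium-to-large effect size (d = 0.7, corresponds to f = 0.35"), and "The sample size was calculated using G*Power 3.1.0". The result is 50 in total, 25 per group. For attrition: "We assume a rather conservative drop-out rate of about 40% from enrolment to follow-up", and so "we propose to start with 80 participants at enrolment (i.e. 40 in the LRT and 40 in the control group"). No design effect or ICC is mentioned.

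**The concern.** Participants who share a therapist tend to have more similar outcomes than participants who do not. Here that similarity can arise through the LRT therapist in one arm only. An ANOVA on participants takes its error term from differences between individuals and treats 40 LRT participants as 40 independent observations. If a handful of therapists produced those outcomes, the LRT mean is less certain than that. The p-value and confidence interval for LRT against control would then be too favourable, and good results from a few therapists could be read as an effect of the manual. The trial also aims to generalise beyond its own setting (Discussion), and for that the therapists should be regarded as a sample of those who might deliver the treatment.

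**Working it through.** **1. The plan's own sample size.** Inputs from the Sample size section: f = 0.35 (d = 0.7), α = 0.05, power 0.80, N = 50.

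- Between-groups effect in a repeated-measures ANOVA, 2 measurements, correlation 0.5 (both assumed): power 0.800 at N = 50 (0.7996 before rounding).
- The same with 3 measurements and correlation 0.6: N = 50, power 0.808.
- One-sided two-sample t-test: N = 52.
- Two-sided two-sample t-test: N = 68, with power 0.68 at 50.

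So 50 can be reproduced with options the article does not state. Every variant that comes close treats participants as independent. On attrition, 50/(1 − 0.40) = 83.3, rounded up to 84; starting with 80 allows a loss of (80 − 50)/80 = 37.5%, which fits about 40%.

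**2. Effect of therapist clustering in one arm.** Let n be the number per arm, k the number of therapists and m = n/k the mean caseload. The documents give n = 25 analysable or 40 enrolled. They give neither k nor the ICC, so both are assumed, with equal or near-equal caseloads.

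- Design effect in the LRT arm: DE = 1 + (m − 1) × ICC
- Factor by which the true standard error of the difference exceeds the ANOVA's: R = √((1 + DE)/2)
- True two-sided error: P(|t| > t₀.₉₇₅ / R), with 2n − 2 degrees of freedom

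Worked case, n = 40, k = 10, ICC = 0.10: m = 4; DE = 1 + 3 × 0.10 = 1.30; R = √(2.30/2) = 1.072; true error 6.7%. Simulating a t-test that ignores therapist gives 7.0%.

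| LRT n | Therapists | m | ICC | DE | R | Error, formula | Error, simulated |
|---|---|---|---|---|---|---|---|
| 25 | 10 | 2.5 | 0.05 | 1.075 | 1.019 | 5.4% | 5.5% |
| 25 | 10 | 2.5 | 0.10 | 1.15 | 1.037 | 5.8% | 6.0% |
| 40 | 10 | 4 | 0.05 | 1.15 | 1.037 | 5.9% | 5.9% |
| 40 | 10 | 4 | 0.10 | 1.30 | 1.072 | 6.7% | 7.0% |
| 40 | 5 | 8 | 0.05 | 1.35 | 1.084 | 7.0% | 7.2% |
| 40 | 5 | 8 | 0.10 | 1.70 | 1.162 | 9.1% | 9.0% |
| 40 | 20 | 2 | 0.05 | 1.05 | 1.012 | 5.3% | 5.3% |
| 40 | 20 | 2 | 0.10 | 1.10 | 1.025 | 5.6% | 5.6% |

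With m = 1, DE = 1 and R = 1 whatever the ICC, so nothing is lost.

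**3. Centres.** A centre effect shared by both arms was simulated under individual randomisation, with 10 centres, 25 or 40 per arm and ICC 0.05 to 0.20. The error of a t-test that ignores centre stayed at 4.9-5.0%. Only variation that falls on the LRT arm alone produces the inflation in step 2.

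**The case against.** The strongest reply is that this argues from silence. The article never says in words that participants are treated as independent, and random effects are often left to an analysis plan, which is not shown here. A therapist level could be present there. That limits how firmly the point can be put. It does not remove it, because the article does not leave the model open: it names the test and lists the covariates.

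The second reply is that the manual, training, monthly supervision and session checklists are there to make therapists alike. They may well lower the ICC. They do not correct the standard error for whatever variation remains.

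The third is that the size is modest and the remedy fragile. Both are fair. If each of the ten centres has at least one therapist (an assumption), the mean caseload is at most 4, and nothing in the protocol suggests as few as five therapists. With 2.5 to 4 participants per therapist, the variance component will be poorly estimated.

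A reader might also infer more than the text supports:

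- That every therapist sees several participants. No caseload is given.
- That therapists are granted latitude in emphasis. The passage on stressing one point more than another is about recording adherence.
- That each centre runs its club in its own way. The protocol says only that all centres offer one.
- That recruiting from ten centres itself makes the standard errors too small. Under individual randomisation a common centre effect does not, as the third step of the working shows.

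**Conclusion.** The point holds for therapists and not for centres. Followed as written, the ANOVA understates the standard error of the LRT-control difference if two conditions are both met: therapists differ, and at least some treat more than one participant. The protocol excludes neither.

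The likely size is modest. With 10 therapists and an ICC of 0.05 to 0.10, a nominal 5% test has a true error of about 5.5-6.0% with 25 LRT completers and 5.9-7.0% with 40 LRT participants. It would reach about 7-9% if only 5 therapists treated 40, and there is no inflation at one participant per therapist. The number of therapists, the caseloads and the ICC behind these figures are all assumptions. The plan would be better for the change, which is cheap, but the trial's conclusions are unlikely to turn on it unless few therapists carry the arm or the result is borderline.

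**What to change.** For the primary endpoints, specify a partially nested mixed model: a random therapist effect in the LRT arm only, control participants unclustered with respect to therapist, the listed covariates kept, and Satterthwaite or Kenward-Roger degrees of freedom. Make it the primary analysis, or at least a prespecified sensitivity analysis beside the ANOVA. State beforehand what will be reported if the therapist variance is estimated at zero. Report the number of therapists, their caseloads and the estimated ICC with its interval. Centre may be added as a precision factor, but this is optional.

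The cost is a few sentences of analysis text. Sessions are already documented in structured form, so therapist identity should be recoverable without new data collection. Confidence intervals will be slightly wider, and with small caseloads the variance component may come out at zero, in which case the model gives little protection beyond the ANOVA. Treatment and assessments do not change.

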### Randomisation

After providing informed consent and receiving a baseline assessment, the participants will be individually assigned to a group at random. The allocation ratio for randomisation into either the treatment or control group is 1:1. The randomisation will be performed by a randomization list that was generated by a computer programme (RandList) beforehand, independently operated by the principal investigator at the University of Siegen, Germany, who does not have any personal contact with the participants. The results of the randomization will be sent to the study coordinator in Jerusalem, Israel, who will contact the therapist to explain the next steps.

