
Outcome variables were assessed using these self-report instruments at three points in time (pretest, posttest, follow-up).

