#### Methods against bias

The proposed study requires several methods to avoid bias.

Selection bias: The randomisation procedure is the gold standard to avoid this bias. Random numbers will therefore be generated in advance. The randomisation procedure will be controlled by comparing the two groups with regard to possible confounders, i.e. age at the time of trauma, gender, educational level, diagnosis, cognitive status and trauma severity.

Detection bias: The baseline assessment is done before randomisation to avoid this bias. In addition, the therapists will not collect any outcome data at posttest and follow-up. This will be done by blinded members of the research team (clinical psychologists or psychiatrists or advanced master students in clinical psychology).

Performance bias: To counteract this bias, the standardisation procedure (manual, extensive training, documentation of sessions, supervision) is established.

Attrition bias: Statistical analysis will include techniques to minimise possible attrition bias, i.e. intention-to-treat analysis and imputing missing data. In case of drop-outs, it is intended to continue data collection whenever possible.

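### The first-named efficacy ANOVA lists five covariates but not the pretest score of the outcome, and so gives up precision the trial could have at no cost

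*Protocol article*

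**What the plan says.** The Statistical analysis section of the protocol article sets out three strategies. The first is an ANOVA comparing mean outcomes for PTSD and depressive symptoms (primary) and for the secondary endpoints. Its covariates are named: "The age at the time of trauma, gender, educational level, cognitive status and trauma severity will be considered as covariates". The second strategy is individual growth curves and the third is multivariate analysis. The section does not say whether the ANOVA takes post-treatment values only or treats time as a repeated factor.

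The pretest score is available. Under Study outcome measures, outcomes are assessed "at three points in time (pretest, posttest, follow-up". The Randomisation and Methods against bias sections both place the baseline assessment before allocation. The second hypothesis under Study objectives expects pretest symptom severity to change the size of the treatment effect, so the plan itself treats that score as relevant.

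The planning figures are in the Sample size section: a "medium-to-large effect size (d = 0.7, corresponds to f = 0.35"), then "Given an α = 0.05 and a test power 1-β = 0.80", giving 50 evaluable participants. It continues: "We assume a rather conservative drop-out rate of about 40% from enrolment to follow-up". Enrolment is set at 80.

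**The concern.** The pretest value of a symptom scale usually predicts its later value well. That is general statistical experience, not a figure in the article. Eligibility spans full or subsyndromal PTSD, depressive, anxiety and prolonged grief disorders, so pretest PCL-5, PHQ-9 and GDS scores can be expected to spread widely. A covariate list without the pretest leaves that spread in the error term, and a chance difference between arms at pretest carries into the comparison of later means.

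Power is at stake in a small trial. So is the reader's confidence that a difference at posttest was not partly there at pretest. The article does not defer the covariates to a later document. It names them, so the omission is a stated choice.

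**Working it through.** **Inputs from the protocol article.** d = 0.7, α = 0.05 (sidedness not stated; two-sided used here), 1:1 allocation, 80 enrolled, 40% drop-out by follow-up. Evaluable at follow-up: 80 × 0.60 = 48, or n = 24 per arm.

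**Assumed.** The correlation r between pretest and later score is shown from 0.3 to 0.8. The variance is taken as equal at both times.

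**The plan's own figure.** A two-sided t-test without pretest needs 34 per arm (68 in total) for 80% power, and at 25 per arm its power is 67.9%. So the stated 50 does not come from a plain two-sided comparison of means. It comes out, exactly or nearly, under variants the article does not state:
- one-sided test: 52
- repeated-measures between-groups test, two measurements, correlation 0.5: 52, with power 80.0% at 50
- pretest-adjusted analysis, r = 0.5: 52, with power 79.9% at 50

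**Formulas.** Power comes from the noncentral t distribution with noncentrality d* × √(n/2).
- Post-treatment means only: d* = d, df = 2n − 2.
- Pretest as covariate: d* = d/√(1 − r²), df = 2n − 3.
- Pre/post group-by-time test, equivalent to a test on change scores: d* = d/√(2(1 − r)), df = 2n − 2.

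**Example at r = 0.5, n = 24.**
- Unadjusted: 0.7 × √12 = 2.425, power 66.1%.
- Adjusted: d* = 0.7/√0.75 = 0.808, and 0.808 × √12 = 2.80, power 78.2%.
- Change score: d* = 0.7/√1 = 0.7, power 66.1%.

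| r | Post only | Pretest-adjusted | Group-by-time (change score) |
|---|---|---|---|
| 0.3 | 66.1% | 70.1% | 51.9% |
| 0.5 | 66.1% | 78.2% | 66.1% |
| 0.6 | 66.1% | 84.3% | 75.6% |
| 0.7 | 66.1% | 91.3% | 86.5% |
| 0.8 | 66.1% | 97.7% | 96.4% |

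**Why the ordering does not depend on r.** The error variance under adjustment is proportional to 1 − r², which is below 1 for any r above 0. Relative to the change score it is (1 − r²)/(2(1 − r)) = (1 + r)/2, which is below 1 for any r below 1. Adjustment costs one degree of freedom. Keeping the five named covariates in the model changes power at 25 per arm by at most about 0.002 if they explain nothing.

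**Chance imbalance.** The standard error of a pretest difference, in SD units, is √(2/n). The probability of a difference of at least 0.3 SD in either direction is about 18% at 40 per arm (0.3/0.224 = 1.34) and about 30% at 24 per arm (0.3/0.289 = 1.04).

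**The case against.** The strongest reply is that the ANOVA may be a repeated-measures one. Three time points are planned, a complete data set is defined by all three, and N = 50 fits a repeated-measures calculation better than a plain two-sided test. The pretest would then be in the model as a level of time, and no one would list it as a covariate. This is a fair reading and it narrows the loss: against the group-by-time test, adjustment gains only 4.8 points at r = 0.7 and 1.3 at r = 0.8. It does not remove the loss, which is 12.1 points at r = 0.5 and 18.2 at r = 0.3. Nor does the fit to 50 help. That calculation takes the full effect at both measurements, which cannot hold if one of them is the pretest.

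The growth curves would naturally include the pretest, as would the planned moderator analyses. That is true, but they are separate analyses and leave the ANOVA as described.

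The size is also uncertain. Follow-up comes about 15 months after pretest (roughly nine of treatment plus six), so r could be low, and at r = 0.3 the gain over a post-only comparison is 4.0 points. Fewer participants will have been lost by posttest, so 24 per arm is a floor there. With an illustrative 32 per arm, unadjusted power is already 78.7%. All of this stands and is why a range is shown.

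A reader might also infer that covariates will be picked after looking at baseline differences, because the five are only to be considered and the Methods against bias section says "The randomisation procedure will be controlled by comparing the two groups with regard to possible confounders". The article does not support this. That comparison is described as a check on randomisation, nothing says covariates will be chosen from it, and the five are named in advance.

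**Conclusion.** The point holds as one of efficiency. The named covariates leave out the pretest score, and either form of the ANOVA is less efficient than a pretest-adjusted comparison. At 24 per arm, d = 0.7 and two-sided 0.05, the gain over a post-only comparison is 4.0 points at r = 0.3, 12.1 at r = 0.5 and 31.6 at r = 0.8. Against the group-by-time test it runs from 18.2 points at r = 0.3 down to 1.3 at r = 0.8. The direction needs only r between 0 and 1, while the size rests on an r that the article does not give.

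A reader might go further and call the planned ANOVA biased. It is not: allocation is randomised, so the unadjusted comparison is unbiased on average. What is given up is precision, and protection against a chance pretest difference in the sample actually drawn. The matter is worth correcting because 50 evaluable participants reach about 80% two-sided power with pretest adjustment at r = 0.5 (79.9%), but 67.9% in a plain comparison of means.

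**What to change.** State that the treatment effect on each outcome is the difference between arms at posttest, and at follow-up, estimated from a model with that outcome's own pretest score as a mandatory covariate, alongside the five covariates already named. In the same sentence, say what form the model takes. If a repeated-measures form is kept, posttest and follow-up should be the repeated outcomes and the pretest a covariate, not a level of time. The baseline comparison can stay as a description of the randomised groups.

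The cost is a change of wording and one degree of freedom per model. No new data, visits or participants are needed, because the pretest is already taken before allocation.

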#### Inclusion and exclusion criteria

Inclusion criteria are:
Being a Holocaust survivor, i.e. born in 1945 or earlier in Europe and having experienced persecution, concentration camp, witnessed torture or death, or been forced to survive in hiding and/or experienced other traumatic events by the Nazi regime during WWII.Diagnosis of full or subsyndromal PTSD, depressive disorder (major depression, minor depression), anxiety disorder, or prolonged grief disorder.Participants do not receive any individual psychotherapy during the time of the study (except for LRT in the intervention condition).Participants must have been informed about the study and must have given written informed consent. This includes that he/she is willing to be randomly assigned to one of the study groups.

Exclusion criteria are: Probable dementia (Mini Mental Status Examination, MMSE < 26); acute psychotic disorder; acute suicidality.

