### Assessment

#### Eligibility screening

Before inclusion into the study, diagnostic interviews are conducted by student research assistants with experience and training in the assessment of PTSD, depression, anxiety disorder, prolonged grief disorder and related disorders, and in the administration of structured interviews. The following self-report measures are used in the context of a clinical interview:
PTSD: The PTSD Checklist for the “Diagnostic and Statistical Manual of Mental Disorders 5” (DSM-5) (PCL-5) is used [29]. It is a 20-item self-report measure that assesses the 20 DSM-5 symptoms of PTSD. It also makes it possible to come to a probable PTSD diagnosis according to DSM-5 criteria [30]. The questionnaire has been found reliable and valid in an Israeli sample [31].Depressive disorder: The Patient Health Questionnaire (PHQ-9) is a widely used 10-item self-report measure of depressive symptoms with well-established psychometric properties [32]. It makes it possible to diagnose a probable major and minor depressive disorder [33] and is sensitive to change [34]. The Hebrew version has also been found to be reliable and valid [35].Prolonged grief disorder is diagnosed according to the criteria proposed for the “International Classification of Diseases 11” (ICD-11) [36]. The validated Hebrew version is used [37].

To screen for potential cognitive impairment, the MMSE [38] in its Hebrew version [39] is used. The clinical work prior to registration will include anamnesis, family history, psychiatric, neurological, internal status and neuropsychological testing (MMSE).

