#### Study outcome measures (primary and secondary endpoints)

All scales are applied in Hebrew language and have been tested for validity and reliability in this language. Primary endpoints are PTSD and depressive symptoms:
PTSD symptoms: The PTSD Checklist for DSM-5 (PCL-5) is used [29] in its Hebrew version [31], a 20-item self-report measure that assesses the 20 DSM-5 symptoms of PTSD.Depressive symptoms: The Patient Health Questionnaire (PHQ-9) and the Geriatric Depression Scale (GDS) are used. The PHQ-9 is a widely used 10-item self-report measure of depressive symptoms with well-established psychometric properties [32] in its Hebrew version [35]. The GDS is a 15-item self-report measure developed for use with older people [40]. It has been found reliable and valid in an Israeli sample [41].

Secondary endpoints are:

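### The ANOVA covariate list omits entry diagnosis, which the protocol itself names as a possible confounder, and also omits the pretest score; the cost is precision, not validity

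*Protocol article*

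**What the plan says.** Three places in the protocol article bear on this.

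- **Statistical analysis.** The first strategy is a set of ANOVAs comparing mean outcomes. The covariate sentence reads: "The age at the time of trauma, gender, educational level, cognitive status and trauma severity will be considered as covariates". That is five variables, the same five as in the Predictors section. The second strategy models individual growth curves.
- **Methods against bias.** "The randomisation procedure will be controlled by comparing the two groups" on six variables, described as "possible confounders, i.e. age at the time of trauma, gender, educational level, diagnosis, cognitive status and trauma severity". Diagnosis is the only item added to the five.
- **Inclusion and exclusion criteria.** Any one of four diagnosis families is enough for entry: "Diagnosis of full or subsyndromal PTSD, depressive disorder (major depression, minor depression), anxiety disorder, or prolonged grief disorder".

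On the endpoints: "Primary endpoints are PTSD and depressive symptoms". PTSD symptoms are measured with the PCL-5, and depressive symptoms with the PHQ-9 and GDS. Under Eligibility screening, the PCL-5 also supplies the PTSD entry diagnosis ("It also makes it possible to come to a probable PTSD diagnosis according to DSM-5 criteria") and the PHQ-9 supplies the depression diagnosis ("It makes it possible to diagnose a probable major and minor depressive disorder"). Outcomes are measured at pretest, posttest and follow-up. The Randomisation section describes individual 1:1 allocation from a computer-generated list and mentions no stratification by diagnosis.

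**The concern.** Someone may enter with PTSD and no depression, with depression and no PTSD, or with neither. Because the entry diagnoses are read from the scales that later serve as primary outcomes, diagnosis separates participants on those scales from the start. The pretest score does so in finer detail. These are probably the two most prognostic baseline variables available, yet neither is in the ANOVA covariate list.

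Two things are at stake. The first is precision, in a trial planned around 50 evaluable participants. The second is the estimate conditional on the allocation that actually occurs. If one arm happens to hold more participants with PTSD, a comparison of post-treatment means that uses neither variable carries that difference. The baseline comparison would show the imbalance, but it corrects nothing, and the plan does not say what follows from it. Since the covariates are only to be considered, it remains open whether the final set is settled before or after that comparison is seen.

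**Working it through.** **1. Inputs from the protocol article.** d = 0.7 (f = 0.35), α = 0.05, power 0.80, 50 required (25 per arm), 80 enrolled (40 per arm), drop-out about 40%.

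**2. Assumed inputs.** The article gives neither the diagnosis mix nor the score gap between diagnoses. Assumed: share with the diagnosis p = 0.3 to 0.5; gap g = 0.5, 1.0 or 1.5 total SD; pre-post correlation r = 0.6.

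**3. The plan's own figure.** For the between-group effect of a repeated-measures ANOVA, λ = f²·N·m / (1 + (m − 1)ρ). With m = 3 and ρ = 0.6, λ = 0.1225 × 50 × 3 / 2.2 = 8.35, and power at N = 50 is 0.808, so 50 is reproduced. The article states neither m nor ρ. A one-sided t-test gives 52. A two-sided t-test gives 68, with power 0.68 at 25 per arm. This matters here because a between-group effect averaged over time carries a level imbalance in full, whereas a group-by-time contrast does not.

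**4. Size of a chance imbalance.** SD = √(2p(1 − p)/n).

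- 40 per arm, p = 0.5: √(0.5/40) = 0.112, so the 95% limit is 1.96 × 0.112 = 0.219.
- 25 per arm, p = 0.5: √(0.5/25) = 0.141, so the 95% limit is 0.277.
- For p = 0.3 the limits are 0.201 and 0.254.

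**5. Shift in a post-treatment comparison using neither variable.** Shift = g × imbalance. At the 95% limit, for p from 0.3 to 0.5:

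| Gap g | 40 per arm | 25 per arm |
|---|---|---|
| 0.5 SD | 0.10–0.11 SD | 0.13–0.14 SD |
| 1.0 SD | 0.20–0.22 SD | 0.25–0.28 SD |
| 1.5 SD | 0.30–0.33 SD | 0.38–0.42 SD |

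**6. What pretest does to the shift.** Take g = 1 and a 20-point imbalance, with the same gap at pretest and posttest.

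- Post score only: 1 × 0.20 = 0.20 SD.
- Pretest as covariate: 0.20 × (1 − 0.6) = 0.08 SD.
- Change score: 0.20 − 0.20 = 0.
- Diagnosis as covariate: 0.

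Simulation (8,000 trials per setting) gave 0.20, 0.08, 0.00 and 0.00.

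**7. Power and error rate** (same simulation: 25 per arm, d = 0.7, p = 0.5, g = 1, r = 0.6, two-sided 0.05):

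| Analysis | SD of estimate | Power |
|---|---|---|
| No covariates | 0.28 | 0.68 |
| Diagnosis | 0.25 | 0.79 |
| Change score | 0.25 | 0.78 |
| Pretest | 0.23 | 0.85 |
| Pretest and diagnosis | 0.22 | 0.87 |

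With no true effect, the rejection rate was about 5% and the mean error about 0 for every analysis, at both 25 and 40 per arm. The planned five-covariate model was not simulated, so the gains are relative to no adjustment.

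**The case against.** **The two lists serve different purposes.** The five covariates are the article's five predictors, and a baseline comparison may cover more than a model adjusts for. The covariate wording is not a closed model either, and a SAP may settle it. That stands so far as calling this a flat contradiction goes. It does not remove the point: the article names a covariate list, and its two most outcome-related baseline variables are not on it.

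**A reader might infer that any diagnosis imbalance passes straight into the PTSD and depression results.** The document does not support that as a general statement. Outcomes are measured at pretest, and the growth-curve strategy models change, which absorbs most or all of a level difference. The qualification is that diagnosis may also alter the rate of improvement, and the Study objectives do expect a larger treatment effect with more severe pretest symptoms. The full shift applies to a comparison of post-treatment means, or of means averaged over time, that ignores pretest.

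**A reader might work from completers only.** With 80 × 0.6 / 2 = 24 per arm and p = 0.5, an imbalance of 20 points or more occurs in about 17% of trials. But intention-to-treat with imputation is planned. At 40 per arm the figure is about 7% (0.20 / 0.112 = 1.79 SD).

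**A reader might take the baseline comparison to be six significance tests**, with 1 − 0.95⁶ = 0.265 as the chance of a false flag if independent. The article mentions no tests, no threshold and no selection of covariates from the result, so that criticism has no text to attach to.

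**Diagnosis is the weaker of the two variables.** This stands. For PTSD and depression it is largely a dichotomised baseline score, and it adds about 2 points of power once pretest is in the model.

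**Conclusion.** The point holds as a matter of efficiency and prespecification. The ANOVA covariate list omits entry diagnosis, which the article itself calls a possible confounder, and omits the pretest score, which matters more. Nothing here makes the test invalid or the estimate biased on average.

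Under the assumed inputs, using no covariates rather than pretest plus diagnosis costs about 19 points of power (0.68 against 0.87), and pretest alone recovers 17 of them. The conditional shift is 0.20 SD per 20-point imbalance without pretest, against a planned effect of 0.7 SD. These sizes depend on the assumed gap, diagnosis share and correlation, none of which the article gives. The shift scales directly with the gap. The gain over the actual five-covariate plan is unknown, and would be smaller to the extent that those five covariates already explain outcome variance.

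**What to change.** In the Statistical analysis section:

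- Prespecify the pretest score of each outcome as a covariate in its ANOVA.
- Add entry diagnosis as two yes/no indicators, one for full or subsyndromal PTSD and one for depressive disorder, so that the list agrees with Methods against bias.
- Replace the tentative covariate wording with a list fixed before outcome data are seen.

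In Methods against bias, state that the baseline comparison is descriptive and does not select covariates.

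The cost is a few lines of text and about three degrees of freedom: one for pretest and two for diagnosis. No new data are needed. The team should expect most of the benefit from the pretest score and little more from diagnosis once pretest is in the model. The case for keeping diagnosis is agreement between the two lists and removal of the residual shift (0.08 SD per 20-point imbalance in the example).
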